### Primary aim

To compare the risk of symptomatic TE in children with or without CVL-dysfunction while receiving therapy for cancer.

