##### Analysis plan

The analysis and reporting of the study will be performed in accordance with the STROBE Statement [50]. The primary outcome is a binary variable- symptomatic TE (presence/absence) as well as a continuous variable (time to event). Independent variables include: age, number of catheter days and time to CVL-dysfunction as continuous variables and, gender (male/female), cancer type, CVL-dysfunction (presence/absence), symptomatic TE (presence/absence), infection (presence/absence) as categorical variables. The process of participant recruitment and retention will be summarized using a flow diagram. Analysis results of participant recruitment and retention will be summarized using descriptive summary measures: mean (standard deviation) or median (minimum-maximum) for continuous variables; and number (percent) for categorical variables. We will use logistic regression analysis to determine the factors that can best discriminate between the two patient groups (i.e. those with and without TE). The list of potential factors is determined *a priori* and includes age of the patient at the time of diagnosis of cancer, cancer type; CVL-dysfunction (presence/absence), infection (presence/absence) and CVL type (internal/external). Univariate analyses will be performed to determine which variables to include in the multivariable models using the criterion of alpha = 0.20. Initially, we will use complete case analysis (i.e. do the analysis without taking missing data into account) and then repeat the analyses with missing data handled by multiple imputation technique [51-53].

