For regression models, we will report the OR (for logistic regression), corresponding standard error, 95% confidence intervals and associated p-values. We will report P-values to 3 decimal places with p-values less than 0.001 reported as p<0.001. For all tests, we will use alpha =0.05 level of significance. Examination of residuals will provide an assessment of model assumptions for regression analyses. Goodnees-of-fit for the models will be performed using appropriate Hosmer-Lemeshov tests. For multivariable regression analysis, we anticipate multicolinearity [54]. We will assess colinearity using the variance inflation factor (VIF) which measures the extent to which the variance of the model coefficients will be inflated (because of the correlation of the variable with other predictor variables) if that variable is included in the model. Variables with VIF >10 will be considered colinear and will be excluded from the analysis [55].

The discriminant performance of the model will be evaluated using sensitivity, specificity and the area under the ROC – receiver operating characteristic curve. We will use bootstrapping approach to internally validate the model. We will compare the performance characteristics (i.e. sensitivity, specificity, area under the ROC curve, etc) between the original model and the bootstrap model. OS and EFS will be estimated using Cox-regression which will allow for adjustment of confounding variables. Hazard ratio (HR) will be calculated using log-rank method.

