##### Sample size

The primary objectives of the study are to develop a model to discriminate between patients with and without symptomatic TE. To determine the optimal discriminant clinical model we will undertake a multivariable analysis. Simulation studies demonstrate that logistic models require 10 to 15 events per predictor to produce stable model estimates [54,55]. Based on our retrospective data and published reports we anticipate that at least 20% patients will be exposed (i.e. with CVL dysfunction) and 80% unexposed (i.e. without CVL dysfunction) [17,33,36]. Preliminary data from the retrospective study showed that the overall prevalence of TE was 11%; 23% of exposed and 9% of unexposed patients had TE. We will evaluate five predictors in our multivariable analysis. In this study, we have a fixed sample size of 450 patients (90 exposed with CVL dysfunction; and 360 without CVL dysfunction). The overall rate of symptomatic TE is assumed to be 11% (~50 events of TE) [36].

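### The univariate screen at alpha 0.20 lets p-values decide which of five pre-listed factors enter the model, does not exempt CVL-dysfunction, and is not clearly covered by the bootstrap validation

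*Protocol article*

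**What the plan says.** The Primary aim is an exposure comparison: "To compare the risk of symptomatic TE in children with or without CVL-dysfunction while receiving therapy for cancer". The Sample size section describes the objective as prediction: "The primary objectives of the study are to develop a model to discriminate between patients with and without symptomatic TE". Both rest on the same logistic regression.

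The Analysis plan names the candidate factors in advance: "age of the patient at the time of diagnosis of cancer, cancer type; CVL-dysfunction (presence/absence), infection (presence/absence) and CVL type (internal/external". The next sentence sets the entry rule: "Univariate analyses will be performed to determine which variables to include in the multivariable models using the criterion of alpha = 0.20". A second removal rule follows: "Variables with VIF >10 will be considered colinear and will be excluded from the analysis". Neither rule makes an exception for CVL-dysfunction. The OR, standard error, 95% confidence interval and p-value are then to be reported from the regression models.

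The Sample size section says "We will evaluate five predictors in our multivariable analysis" and relates about 50 expected TE events to a requirement of 10 to 15 events per predictor.

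For internal validation by bootstrap, the Analysis plan says: "We will compare the performance characteristics (i.e. sensitivity, specificity, area under the ROC curve, etc) between the original model and the bootstrap model". It does not say on which data the bootstrap model is scored, or whether the screen is rerun in each resample.

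**The concern.** The primary question concerns one variable, and the rule as written allows the data to remove that variable from the adjusted model. If that happened, no adjusted estimate would exist for the primary hypothesis. The same rule can remove a factor that is related to both dysfunction and TE, because a univariate p-value is not a test of confounding.

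When the outcome data choose the model, the usual standard errors and p-values treat that model as if it had been fixed beforehand, and the apparent AUC is too high. The Discussion intends the result to identify high-risk children for later anticoagulation trials, so overstated discrimination would carry forward into their planning.

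**Working it through.** **1. The plan's own event count.** 450 × 0.11 = 49.5, which reproduces the stated figure of about 50. Per predictor: 49.5 / 5 = 9.9. From the group rates: 90 × 0.23 + 360 × 0.09 = 20.7 + 32.4 = 53.1 events, or 10.6 per predictor. The lower bound of 10 is essentially met with all five factors in the model, provided each uses one parameter. The screen is therefore not needed to meet it.

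**2. Chance that CVL-dysfunction fails the screen.** Inputs: n1 = 90 exposed and n0 = 360 unexposed (Sample size); two-sided p < 0.20, so z = 1.2816 (two-sidedness is assumed).

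- SE0 = √[p̄(1−p̄)(1/n1 + 1/n0)]
- SE1 = √[p1(1−p1)/n1 + p0(1−p0)/n0]
- d = p1 − p0; c = 1.2816 × SE0
- P(dropped) = 1 − Φ((d−c)/SE1) − Φ((−d−c)/SE1)

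At the protocol's 23% versus 9% (OR = (0.23/0.77)/(0.09/0.91) = 3.02): p̄ = 0.118, SE0 = 0.0380, c = 0.0487, SE1 = 0.0469. Then (0.14 − 0.0487)/0.0469 = 1.95, and P(dropped) = 2.6%.

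For other true ORs, with overall TE held at 11% (SE0 = 0.0369, c = 0.0473):

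| True OR | TE exposed / unexposed | P(dropped) |
|---|---|---|
| 3.0 | 21.5% / 8.4% | 3% |
| 2.5 | 19.6% / 8.9% | 9% |
| 2.2 | 18.2% / 9.2% | 16% |
| 2.0 | 17.2% / 9.4% | 23% |
| 1.5 | 14.5% / 10.1% | 53% |

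The choice of test and approximation moves the OR 2.0 figure between about 21% and 24%.

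**3. Chance that another binary factor fails.** Same formula, overall TE 11%. Prevalence is an assumption, since the article gives none.

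| True OR | Prevalence 30% | 40% | 50% |
|---|---|---|---|
| 2.2 | 11.4% | 10.0% | 10.5% |
| 2.0 | 18% | 16% | 17% |
| 1.5 | 48% | 47% | 48% |

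OR 2.2 is the value that the Rationale for secondary aim 1 cites for infection.

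**4. What the bootstrap would show under three readings.** Simulation of 450 patients at 11% TE with the 0.20 screen, 150 data sets and 60 resamples each. Assumed: cancer type in four levels, infection prevalence 40% and related to dysfunction, modest effects for age and CVL type.

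| | Dysfunction OR 3, infection OR 2.2 | Both OR 1.5 |
|---|---|---|
| Apparent AUC | 0.706 | 0.617 |
| True AUC | 0.670 | 0.557 |
| True optimism | 0.036 | 0.060 |
| Mean AUC of bootstrap models in their own resamples | 0.714 | 0.627 |
| Optimism estimated, selected variables held fixed | 0.017 | 0.020 |
| Optimism estimated, screen repeated | 0.038 | 0.058 |

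A side-by-side comparison (0.714 against 0.706; 0.627 against 0.617) shows no loss. Holding the selected variables fixed recovers about half of the optimism or less. Repeating the screen recovers nearly all of it.

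**5. Parameters if cancer type has several levels.** With four levels, as an example, it uses three parameters and the full model seven: 49.5 / 7 = 7.1 events per parameter, or 53.1 / 7 = 7.6 from the group rates.

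**The case against.** Several points on the other side are sound.

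- **Loss of the exposure.** A reader might infer that CVL-dysfunction is likely to be screened out. The documents do not support that: at the planning rates the chance is 2-3%, and the Rationale for secondary aim 3 cites OR 3.7 from an earlier paediatric study. If the exposure did fail at 0.20, the unadjusted result would already be non-significant at 0.05 and would still be available; only the adjusted estimate would be lost.
- **Bootstrap.** A reader might infer that the planned validation cannot detect overfitting. The text does not establish this. It leaves the procedure open, and a bootstrap that repeats the screen works well. Resampling detail is also something an article may leave to a fuller document. What stands is that the one comparison it does specify can be read in a way that shows nothing.
- **Contradiction.** The five are described as potential factors, and evaluating five predictors can mean screening five candidates. The two sections sit badly together but do not flatly conflict.
- **Size of confounding.** A factor that fails the screen has a weak association with TE in that sample. In a simulation with dysfunction OR 3 and one binary confounder (35% prevalence in the unexposed, OR 2 with dysfunction, OR 1.5 to 2.2 with TE), dropping it changed the dysfunction OR by 0.7% to 1.6% on average, with 95% of differences between about −7% and +5%. The bias from one such factor is small.
- **VIF.** A VIF above 10 for dysfunction needs an R² above 0.90 on the other four factors. Nothing suggests this; the rule merely lacks the same exemption.
- **Forcing in all five.** The Abstract and the Rationale for secondary aim 3 treat infection as a possible consequence of dysfunction, so adjusting for it may remove part of the effect of interest. Cancer type can also use more than one parameter. Both points change the remedy.

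None of this gives the screen a purpose. It still lets the outcome data choose the model while the reported inference ignores that choice.

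**Conclusion.** The point holds in limited form. The article states a rule, not a gap: p-values at 0.20 decide entry for five pre-listed factors, and the primary exposure is not exempted. The risk to the exposure is about 2-3% under the planning rates and becomes material only if the true OR is near 2 or below (about 21-24% at 2.0, about 53% at 1.5). A factor with OR 2.2 is lost in about 10-12% of studies at the assumed prevalence of 30-50%. In the simulated settings, optimism in the AUC was 0.036 to 0.060; whether the planned bootstrap would reveal it depends on a procedure that the article does not fix. The drop probabilities assume a two-sided test and, apart from the 23% versus 9% case, 11% TE overall. The AUC figures rest on assumed effects and covariate distributions. This is worth correcting before analysis but does not threaten the study.

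**What to change.** 1. Delete the univariate screen and fit the pre-specified factors in one model. State that CVL-dysfunction is always retained, including under the VIF rule.
2. Group cancer type in advance into few categories and state the resulting events per parameter, acknowledging that it falls below 10 if cancer type uses more than one parameter.
3. Report the dysfunction OR with and without infection in the model, because infection may lie on the path from dysfunction to TE.
4. Report an optimism-corrected AUC: in each bootstrap sample repeat any data-driven step that is retained, score that model in the resample and in the original data, and subtract the average difference from the apparent AUC.

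Only the analysis wording changes; no new data are needed. The price is slightly wider intervals and a slightly less favourable AUC.

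### The only named goodness-of-fit test for the TE model, Hosmer-Lemeshow, has low power against many misfits at about 50 events and cannot show overfitting; no calibration estimate is named

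*Protocol article*

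**What the plan says.** The Sample size section makes a multivariable model that separates patients with and without symptomatic TE the primary objective, and it gives the scale: a cohort of 450, of whom 90 are expected to be exposed and 360 not. On events it says "The overall rate of symptomatic TE is assumed to be 11% (~50 events of TE"), and on the size of the model "We will evaluate five predictors in our multivariable analysis".

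The Analysis plan lists the five candidates: age at diagnosis, cancer type, CVL-dysfunction, infection and CVL type. On the adequacy of the model it says four things:

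- Residuals: "Examination of residuals will provide an assessment of model assumptions for regression analyses".
- Goodness of fit: "Goodnees-of-fit for the models will be performed using appropriate Hosmer-Lemeshov tests". The number of risk groups is not given. The general rule is "For all tests, we will use alpha =0.05 level of significance".
- Performance: "The discriminant performance of the model will be evaluated using sensitivity, specificity and the area under the ROC" curve.
- Validation: "We will use bootstrapping approach to internally validate the model". The original and bootstrap models are compared on those same three measures, in a list that ends open.

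No calibration slope, calibration plot or other estimate of the gap between predicted and observed risk is named. No rule says what follows from a significant or a non-significant Hosmer-Lemeshow result.

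**The concern.** A goodness-of-fit test can reject a model but cannot confirm it. How much a non-significant result is worth depends on the test's power, and about 50 events is few for a test that spreads them over several risk groups. The test is also computed on the data used to fit the model, so it cannot see predictions that are too extreme because of overfitting. Sensitivity, specificity and ROC area do not fill the gap: they describe ranking and classification, not whether a predicted risk of, say, 20% is right.

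The Discussion wants to identify children at high risk of TE, sets this beside a 5-15% bleeding risk under anticoagulation, and plans later diagnostic studies and a randomised trial from the results. If predicted risks from the model are carried into that planning, their calibration matters. Two possible misfits arise from the document itself. The Secondary hypotheses section proposes that dysfunction and infection together raise TE risk, yet the predictor list has no interaction. Age is listed as continuous with no check for non-linearity, although the Background reports more CVL complications in younger children.

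**Working it through.** **1. The plan's own figures.** 450 × 0.11 = 49.5 events, matching the stated figure of about 50. Per predictor: 49.5 / 5 = 9.9. From the subgroup rates: 0.23 × 90 + 0.09 × 360 = 20.7 + 32.4 = 53.1 events (53.1 / 450 = 11.8%). With ten risk groups, each holds 450 / 10 = 45 patients and on average 49.5 / 10 = 4.95 events.

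**2. The statistic.** The sum over g groups of (O − E)² / [E(1 − E/n)], where O and E are observed and expected events, referred to chi-square on g − 2 df at alpha 0.05.

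**3. Power by simulation.** From the document: N = 450, mean risk 11%, five predictors, dysfunction in 20%. Assumed, because the document does not give them: age uniform over 0-18 years, infection 40%, leukemia 45% (cancer type in two classes), external CVL 50%, and all misfit shapes. The fitted model has main effects and linear age. There were 3000 runs per scenario, so the Monte Carlo standard error is at most √(0.5 × 0.5 / 3000) = 0.9 points. Ten groups:

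| True model | Rejected | Largest decile error in mean risk (points) |
|---|---|---|
| Main effects, linear age (fit correct) | 4.3% | 0.5 |
| Dysfunction × infection from the ORs in the rationale for secondary aim 3 (3.7, 2.2, both 6.4) | 3.3% | 1.1 |
| Dysfunction × infection, interaction OR 4 | 10.5% | 5.9 |
| Age × dysfunction, crossover | 17.4% | 6.3 |
| Cancer type × CVL type, crossover OR 6 | 19.1% | 8.6 |
| Age thresholds, OR 4-6 | 4.4-7.7% | 0.9-1.1 |
| Symmetric U in age, quadratic 0.4 / 0.7 / 1.0 / 1.5 per SD² | 4.2 / 8.6 / 16.5 / 28.6% | 0.5-1.8 |
| Age linear 0.3, quadratic 0.4 / 0.7 / 1.0 | 6.5 / 12.7 / 22.3% | 1.2-2.4 |
| Age linear 0.5, same quadratics | 8.4 / 17.5 / 37.8% | 1.6-5.2 |
| Age linear 0.8, same quadratics | 13.1 / 34.4 / 66.0% | 2.7-9.4 |

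With six groups the rates differ by at most about 8 points. A separate set of 2000 runs per scenario used four cancer groups (seven coefficients) and gave: correct model 3.8%; dysfunction and infection acting only in combination (OR 8) 14.7%; omitted interaction OR 3 8.6%; U-shaped age 4.8%; age step OR 4 6.5%. A further check gave 13% and 8% for the two interaction cases, with decile errors of about 6 and 3 points, and 4-7% for the age cases.

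**4. A contrasting case.** With one continuous predictor only, power is much higher: 31%, 83% and 99% for quadratics 0.4, 0.7 and 1.0, and 21% for a threshold of OR 4.

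**5. Overfitting.** A logistic model fitted by maximum likelihood has slope 1 in its own sample by construction. Under the same kind of assumptions, the slope in the population is about 0.75 to 0.83. To illustrate (both the predicted value and the anchor at the 11% average are chosen for the example), take a predicted risk of 30%. Then logit 0.30 = −0.847, logit 0.11 = −2.091, and the difference is 1.243.

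- Slope 0.75: −2.091 + 0.75 × 1.243 = −1.158, a risk of 23.9%.
- Slope 0.83: −2.091 + 0.83 × 1.243 = −1.059, a risk of 25.8%.

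**6. What the slope does not show.** In 150 simulated data sets with 40 resamples each, the mean optimism-corrected slope was 0.79 for the correct model. It was 0.78 (combination OR 8), 0.87 (interaction OR 3), 0.79 (U-shaped age) and 0.83 (age step) for the wrong ones. It measures overfitting and does not separate right from wrong functional form.

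**The case against.** Much of the case on the other side stands.

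- The Analysis plan never says that p > 0.05 means the model fits, and no decision hangs on the test. A reader might infer such a rule from a goodness-of-fit test read at alpha 0.05, but the text does not contain it.
- The test is not alone. Examination of residuals is planned in the sentence just before it, and residuals can reveal a wrong form for age. They are not an estimate of miscalibration.
- The published odds ratios do not point to a strong interaction. If 3.7 and 2.2 are read as separate effects, 3.7 × 2.2 = 8.1, which exceeds 6.4. The resulting misfit is trivial (mean absolute risk error 0.005), so non-rejection there is no failure.
- The age-threshold and symmetric U-shaped misfits barely disturb risk-group calibration (at most 1.8 points by decile). Individual risks are wrong, but the test is not missing much of what it measures. The interaction cases, with decile errors of about 3 to 9 points, are the fairer illustration.
- The stated goals are discrimination and a comparison by dysfunction status, and the bleeding figure in the Discussion is background.

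It can also be said that an article may leave calibration reporting to a fuller plan. That is fair for detail. It is less persuasive here because the article does name its fit test and its performance measures, and nothing named estimates calibration.

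**Conclusion.** The point holds as a minor one. Hosmer-Lemeshow is the only goodness-of-fit test named, and at about 50 events its power against the assumed misfits of a five-predictor model is roughly 3% to 66%, with 4% to 19% for most interaction and age-threshold cases. It is blind to overfitting, which plausibly puts the slope at about 0.75 to 0.83. A non-significant result would be weak evidence that predicted risks are right.

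These figures rest on assumed covariate distributions, effect sizes and misfit shapes, and on fitting all five predictors without the planned univariate screening. A reader might infer a floor on the miss rate, such as 85% or more of serious misfit. The documents do not support that: they define no serious misfit and set no power target for this test. In the five-predictor simulations the miss rate falls as low as 34% (100 − 66), and close to zero when one continuous predictor dominates. Nor does the point undermine the primary comparison of TE risk by dysfunction status.

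**What to change.** In the Analysis plan:

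1. Within the bootstrap already planned, report the optimism-corrected calibration slope with its confidence interval and a smoothed, optimism-corrected calibration plot. Repeat the univariate screening in each resample, so that the slope reflects the whole model-building procedure.
2. If the Hosmer-Lemeshow test is kept, give the number of groups and state that a non-significant result is not evidence of fit.
3. Because the slope does not detect wrong form, add a sensitivity analysis of form: a restricted cubic spline for age and the dysfunction-by-infection term that the Secondary hypotheses section implies. Report estimates with intervals, since about 50 events will leave them imprecise.

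In-sample calibration-in-the-large is not worth adding, as it is zero by construction.

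The cost is a few sentences and a little code in the existing bootstrap, with some extra computing for the interval; no new data are needed. The downside is that reported calibration will look less favourable than a non-significant p-value.

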### Secondary aims

In children receiving therapy for cancer,

1. To compare the prevalence of infection at any site in children with or without CVL-dysfunction

2. To compare the five-year OS and EFS in children with or without CVL-dysfunction

3. To delineate the relationship of CVL-dysfunction, infection and TE

4. To evaluate the impact of different CVL-related (type, insertion techniques, care guidelines) and patient-related (age, height, body mass index) factors on the development of CVL-dysfunction, TE and infection

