### Patient eligibility

#### Inclusion criteria

All children (≤ 18 years of age) newly diagnosed with non-CNS cancer will be eligible for the proposed study. Not all patients with CNS cancers receive CVL and the prevalence of TE in children with brain tumors is very low (< 2%) [32,36,46]. Hence we will include only children with non-CNS cancers.

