### Strengths and potential limitations of the study

The major strength of the study is the use of a prospective cohort design. Previous studies were single institution studies using retrospective design [17,32,33,36]. These studies report up to 30% of missing data [17,32,33,36]. To avoid this problem we will use uniform data collection forms for all study participants and for patients with TE which is likely to capture all the relevant information. Further, the CVL access data will be collected prospectively and hence the exposure criteria will be recorded properly avoiding any recall bias.

Unlike previous studies, evaluation of CVL-dysfunction is the primary aim of our study which formed the basis of our sample size calculation. By inclusion of only symptomatic and objectively confirmed TE, we will avoid ambiguity over diagnosis, and thus, reporting of TE. Uniform guidelines for diagnosis and evaluation will likely minimize chances of misdiagnosis of TE.

In addition the following steps are taken to minimize sources of errors and likely biases improving internal validity of the study. To avoid selection bias all consecutive newly diagnosed non-CNS cancer patients meeting the inclusion criteria will be eligible and approached for participation in the proposed study. All reported events of TE will be confirmed by an independent adjudication committee. To avoid recall bias CVL access data will be collected prospectively and hence the exposure criteria will be recorded properly. Assessors (radiologists) evaluating for TE will be blinded as regards the “exposure” status to avoid measurement bias. With the use of uniform data collection forms for all study participants and patients with TE, infection and CVL dysfunction, all the relevant information is likely to be captured. Further, all data will be analyzed centrally.

Another strength of the study is that this study is conducted across five pediatric oncology institutions with inclusion of wide range of cancer diagnoses. Hence we think that the findings of the study will be generalizable to pediatric oncology population. The results of this study will also be applicable for adults with cancer as well as to the population of patients with other chronic diseases who need long term CVL.

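### The VIF >10 exclusion rule has no removal order and no protected variables, so it can drop both age and height from a secondary aim 4 model

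*Protocol article*

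**What the plan says.** The rule is in the Analysis plan. It is introduced for multivariable regression in general: "For multivariable regression analysis, we anticipate multicolinearity". The action follows: "Variables with VIF >10 will be considered colinear and will be excluded from the analysis". The text names no variable that is exempt, no sequence of removal, no recomputation after a removal, and no treatment of factors with several levels.

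Secondary aim 4 sets out to evaluate CVL-related factors together with "patient-related (age, height, body mass index) factors on the development of CVL-dysfunction, TE and infection". Eligibility covers the whole of childhood: "All children (≤ 18 years of age) newly diagnosed with non-CNS cancer will be eligible".

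The protocol writes out no regression model for aim 4. The one factor list it specifies is for the TE model and "includes age of the patient at the time of diagnosis of cancer, cancer type; CVL-dysfunction (presence/absence), infection (presence/absence) and CVL type (internal/external"). Neither height nor BMI is on that list. A screen comes first: "Univariate analyses will be performed to determine which variables to include in the multivariable models using the criterion of alpha = 0.20".

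**The concern.** Collinearity belongs to a set of variables, so both members of a collinear pair carry the high VIF. A rule that excludes every variable above the cut removes both, although taking out one is enough. Age and height over 0 to 18 years are an obvious candidate pair, and aim 4 names both.

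If both go, aim 4 loses the multivariable estimates for two of its three patient factors. The comparisons of CVL type, insertion technique and care would also be made without adjustment for age. The section on the significance of CVL dysfunction reports more CVL complications in younger children, and the rationale for aim 4 hopes to derive CVL-care guidelines from these comparisons. How much bias would follow depends on whether age differs between the CVL groups, which the protocol does not report.

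A second, smaller worry is cancer type. The VIF of an indicator variable depends on which level is the reference, so a fixed cut-off can be triggered by coding.

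**Working it through.** **Inputs from the protocol.** Cut-off VIF >10 (Analysis plan); age up to 18 years (Inclusion criteria); "we have a fixed sample size of 450 patients (90 exposed with CVL dysfunction; and 360 without CVL dysfunction") (Sample size); cancer type is categorical, in a cohort "with inclusion of wide range of cancer diagnoses", with levels and reference not stated. **Not in the protocol:** the age-height correlation r. It is assumed below, over a range.

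**The plan's own figure.** The protocol gives no VIF. Its event count reproduces: 450 × 0.11 = 49.5, stated as about 50, or 49.5 / 5 = 9.9 events per predictor. This bears on the point only by confirming that the TE model has five predictors.

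**Step 1: where the cut falls.** VIF = 1/(1 − R²), where R² comes from regressing the variable on the other predictors. VIF >10 means R² > 0.90. For two variables alone both VIFs equal 1/(1 − r²), so the cut is |r| > √0.90 = 0.949.

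| r | VIF of each |
|---|---|
| 0.90 | 5.3 |
| 0.94 | 8.6 |
| 0.95 | 10.3 |
| 0.96 | 12.8 |
| 0.97 | 16.9 |

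**Step 2: sampling variation at n = 450.** For a simulated bivariate normal pair, the chance that the sample VIF exceeds 10 is 0% at r = 0.93, 5% at 0.94, 62% at 0.95 and over 99% at 0.96. The outcome turns on a narrow band of r.

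**Step 3: plausible r over 0 to 18 years (assumed growth).**

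- Height from about 50 cm at birth to about 170 cm at 18 years, within-age SD 2 to 7.5 cm: r about 0.97, VIF about 17 to 20, above 10 in all simulated samples of 450. With SDs enlarged by half: VIF 10.5 to 11.8, both above 10 in 72% to 90% of samples.
- Sex-specific growth: VIF about 14 to 17, above 10 in all samples. With SDs enlarged by half: VIF 9.4 to 10.5, above 10 in 21% to 70% of samples.
- A wider grid of 60 scenarios (50 to 170 cm, within-age SD 4 to 10 cm, five growth curvatures, three age mixes, BMI also in the model): r from 0.89 to 0.99, VIF from 5 to 77. Age and height were nearly equal each time (for example 17.6 and 17.1). In 16 of the 60 both stayed below 10. BMI stayed at 1.1 to 1.2.

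**Step 4: remove one only.** With height taken out and VIF recomputed, the VIF of age was 1.1 to 1.2 in every scenario of the grid, so age would stay. With height and BMI as age-standardised scores, simulated VIF was 1.00. That value follows from generating the scores independently of age, so real data may give slightly more.

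**Step 5: cancer type.** For a factor with at least three levels, taken alone, with reference share p₀ and level share pⱼ:

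VIF = (1 − pⱼ)(p₀ + pⱼ)/p₀, with maximum (1 + p₀)²/(4p₀) at pⱼ = (1 − p₀)/2.

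- Setting the maximum to 10 gives p₀² − 38p₀ + 1 = 0, so p₀ = 19 − √360 = 0.0263. Then 0.0263 × 450 = 11.8, that is, at most 11 patients.
- A 40% level against a 2% reference: 0.60 × 0.42 / 0.02 = 12.6. Against a 10% reference: 0.60 × 0.50 / 0.10 = 3.0. The maximum at a 5% reference is 5.5.
- Assumed example with levels of 9, 180, 90, 81 and 90 patients: with the 9-patient level as reference the VIFs are 12.6, 8.8, 8.2 and 8.8; with the 180-patient level as reference they are 1.03 to 1.20.

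**The case against.** The strongest reply is that the affected model is not on the page. Aim 4 names age, height and BMI as factors to evaluate, but does not say that they enter one model. Height and BMI are missing from the listed independent variables and from the TE factor list. How aim 4 covariates are combined may be settled in a fuller document. This stands as a condition: the point applies only where age and height share a model. The exclusion rule itself is stated, without limits, for multivariable regression.

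Second, the rule need not be read as removing all flagged variables at once. The plan explains VIF as the inflation caused by including a given variable, which is compatible with checking one variable at a time, and then age would survive. That is a fair reading, but the text does not require it, and an analyst who followed the sentence literally would delete both.

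Third, both variables must first pass the 0.20 univariate screen. That is also a condition, but weak protection: near-duplicate variables tend to pass or fail together. The univariate results would still be available, so the factors would not go wholly unexamined; they would lack adjusted estimates.

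Fourth, a cut-off of 10 is common, and standardised height answers a different question. The protocol explains complications in younger children by vessel size, which concerns absolute body size. This stands as a cost of the preferred repair.

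**Conclusion.** The point holds for secondary aim 4, conditionally. If age and height enter the same model and r exceeds about 0.95, the literal rule removes both when removing one would do. Under assumed ordinary growth this is likely (VIF about 14 to 20); with wider within-age spread it is close to even (VIF about 9 to 12). The algebra is certain. The size rests on growth assumptions that the protocol does not supply.

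A reader might infer three stronger things, and the protocol supports none of them:

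- That age and height are bound to be removed. No correlation is given, no aim 4 model is written out, the 0.20 screen comes first, and 16 of 60 assumed scenarios left both below 10.
- That the primary analysis is damaged. The five-factor TE model has no height, so this pair cannot arise there. The sample size is untouched.
- That cancer type as a whole would be lost. This route needs at least three levels, a reference of at most 11 of 450 patients and another large level. In the example one indicator of four crosses the cut. Dropping it would merge that level with the reference and leave the rest of the factor in place.

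This is a correction worth making for a secondary aim, with the cancer-type issue a minor addition.

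**What to change.** Replace the exclusion sentence in the Analysis plan with wording to this effect:

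1. VIF will be reported for each multivariable model. CVL-dysfunction, the a priori factors and the aim 4 factors will not be removed because of VIF.
2. Where age and height are in the same model, height and BMI will be entered as age- and sex-standardised scores. If raw height is preferred, one variable of the pair will be removed at a time, in an order fixed in advance, with VIF recomputed after each removal.
3. Collinearity of cancer type will be assessed for the factor as a whole by generalised VIF, with the largest group as reference.

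The raw-height alternative in item 2 is an exception to item 1 and should be written as one; since age is an a priori factor, it would be the one kept.

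The cost is a few sentences and the choice of a growth reference. Height and BMI are already aim 4 variables, and gender is already an independent variable, so no new data are needed. The downside is that the height coefficient is then read as height relative to age, not absolute size. Protection from removal on VIF also does not protect a factor from the 0.20 univariate screen; if the a priori and aim 4 factors are meant to stay, the plan should say so there as well.
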